### Implementation outcome measures

To examine reach, we will assess the proportion of patients offered trial enrollment and the proportion enrolled out of the number of eligible patients who had a visit during the recruitment period (Fig. 1). We will examine the adoption of the provider prompt (% of messages opened by the receiving provider) and fidelity of the patient component (coding a random selection of phone sessions to assess presence/absence of behavioral targets). To understand the contextual factors related to the feasibility and acceptability of the strategies [52], in pre- and post-study, we will conduct semi-structured interviews with stakeholders across the MedStar primary care network including at the 4 study clinics. Finally, we will randomly select 30 study participants (15 Black/African American, 15 White; patients who received a LCS order and completed it and those who received a LCS order and did not complete it) to conduct in-depth interviews at 6 months to assess perceptions of the quality of the patient inreach and education, the impact of the implementation strategy, and suggestions for improvement.

### Sample size and power

All power calculations were performed for the primary outcomes (provider-patient discussion, screening intentions, and knowledge), using intention-to-treat principles, and a significance level of 0.05. We will have 83% power to detect a difference of 12% for the provider-patient screening discussion, a difference of 15% for likely screening intention, and an effect size of 0.33 for the screening knowledge score. For the moderation analyses, we will have > 80% power to detect an effect size of 0.50 with equal subgroups (e.g., Black vs White, high vs. low literacy levels).

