### Patient recruitment and procedures

During the recruitment period, the research assistants will access the list of potentially eligible individuals from an EHR report that our team developed to identify patients with an upcoming visit who are 50–80 years old with an ever-smoking history. Due to the limitations of the EHR smoking history data, including a large number of missing data for the pack-years field (90% on average are missing pack-years), we are conservatively estimating 25% of those reached will be eligible for the study (Fig. 2). The report utilizes EHR appointment and clinical data and will be imported into the study’s REDCap database weekly by the study team. Our team will invite patients to participate in the study through a mailed invitation letter, email, and the myMedStar patient portal, followed by phone calls (up to 3 attempts). During this call, the research staff member will describe the study, determine eligibility, obtain verbal consent, and complete the baseline assessment. We expect to enroll *n* = 184 in the Multilevel Clinics and *n* = 184 in the Comparison Clinics (total *N* = 368).

Following baseline (T0), Multilevel Clinic participants will receive the phone-based inreach and education within 1 week to 3 days prior to the visit. The comparison clinics will not receive the bundled strategies, but eligible participants will be enrolled and followed to measure the outcomes. All patient participants will receive up to $50 in total for their participation.

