### Measures

We will use mixed-methods and multilevel assessments (Table 1). At the *patient-level*, participants will be assessed at baseline and 1-week post-visit to measure the primary outcomes: provider-patient discussion (“Did you have a discussion with your doctor about lung screening?”), screening intentions (“Do you plan to have a CT scan to check for lung cancer in the next 6 months?”), and knowledge using 11 true/false items from the literature [47]. We will administer the Questionnaire on the Quality of Physician–Patient Interaction scale to measure patient-reported provider-patient communication [48]. The Lung Screening Health Beliefs Scale will measure perceived risk, self-efficacy, benefits, and barriers [49]. The Consumer Health Activation Index will be administered to measure patient activation [35]. We will evaluate potential moderators including race (non-Hispanic African American vs. non-Hispanic White vs. other), smoking status (current vs. former), and health literacy (“How often do you find numbers, figures, or graphs to be useful in making a health-related decision?”) [50].

**Table 1 Tab1:** Complete measures

		**T0**	**T1**	**T2**
		**Baseline**	**1 week**	**6 months**
***Patient-level variables***	*Primary outcomes*: Provider-patient discussion, lung screening intentions, screening knowledge	**X**	**X**	
	*Secondary outcomes*: Lung screening referrals, completion rates (EHR)	**X**		**X**
	*Moderators*: Race, smoking status, health literacy	**X**		
	*Intervention targets*: Physician–patient communication, perceived risk, self-efficacy, benefits/barriers, patient activation, attended visit/visit type	**X**	**X**	
	*Covariates*: Demographics, social determinants of health, tobacco behaviors, cancer screening history, psychological variables (e.g., stigma, medical mistrust)	**X**		
***Provider-level variables***	Demographics	**X**		
	Lung screening practices	**X**		**X**
	Lung screening attitudes	**X**		**X**
	Intervention acceptability, usability, intervention, effectiveness			**X**
***Implementation variables***	Reach: % of patients offered trial enrollment and the % enrolled out of the number of eligible patients who had a visit during the recruitment period	**Pre-post implementation**		
	Effectiveness: screening referrals and screening completion rates			
	Adoption: % of messages opened by the receiving provider; fidelity of the patient component			
	Implementation: feasibility, acceptability			

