### Statistical analysis plan

We will examine the distributions of all variables to describe the characteristics of the study population. We will conduct analyses using *t*-tests, *χ*^2^ tests, and Pearson or Spearman correlation coefficients to assess the bivariate associations between the baseline characteristics and the outcome variables. Bivariate analyses will also be conducted to assess the associations between the study arm and baseline characteristics. Owing to any significant differences detected at the 0.05 level, the variables associated with both the study arm and the outcome of interest will be entered as covariates in subsequent analyses. To test the overall difference between the study arms on the primary outcomes, we will conduct logistic regression models (for provider-patient discussion — yes/no, screening intentions — likely/unlikely) and a linear regression model (for the screening knowledge score). Logistic regression analyses will also be conducted on the secondary screening outcomes (lung screening referral — yes/no, lung screening completion — yes/no). This study will explore potential moderators (e.g., race, health literacy, smoking status). That will be done by evaluating the presence of interactions between the moderators and study arm, one at a time, after adding them to the regression models described above. In sensitivity analyses, we will evaluate the robustness of our findings by using versions of the above models with generalized estimating equations (GEE). These models will use the sites as clusters, and assume an exchangeable working correlation structure.

For the qualitative analysis, we will use a deductive thematic analysis based on a priori PRISM constructs, with additional codes added as needed. Initial codes will be generated by two coders and each of the coders will review two transcripts for each sub-population (i.e., patient and provider) to reach a consensus on the coding framework and application of codes prior to splitting up the remaining transcripts.

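### The power of more than 80% stated for moderation is not reached by the planned interaction test: about 60–67% for the knowledge score if 0.50 is a difference of arm effects in SD units

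*Protocol article*

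**What the plan says.** Under Sample size and power, the protocol states that "All power calculations were performed for the primary outcomes" (discussion, intentions and knowledge), with "a significance level of 0.05". For the overall comparison it gives 83% power, including for "an effect size of 0.33 for the screening knowledge score". For moderation it claims more than 80% "power to detect an effect size of 0.50 with equal subgroups", with Black versus White and high versus low literacy as examples. It does not define the 0.50, name the test, or state an analysed number, sidedness or covariate gain.

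Under Statistical analysis plan, moderation is examined by "evaluating the presence of interactions between the moderators and study arm, one at a time", added to the regression models for the outcomes. Under Study aims, the race example expects a knowledge gain from the strategies among African American participants and a smaller impact among White participants, which is a contrast of two arm effects.

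Under Measures, the race moderator has three levels: "race (non-Hispanic African American vs. non-Hispanic White vs. other". Under Clinical setting and healthcare provider participants, the clinics' populations are given as 44–73% Black or African American. Planned enrolment is 184 per arm, 368 in total.

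**The concern.** An interaction is a difference of two differences. With four equal cells its variance is twice that of the arm difference inside one of the two subgroups, and four times that of the overall arm difference. A study with 83% power for an overall effect of 0.33 SD would need an interaction of about 0.66 SD for the same power. A claim of more than 80% at 0.50 is therefore doubtful on its face.

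Whether the strategies work differently in Black and White patients is the equity question the study sets out to explore. If the true difference in effects were 0.50 SD, the printed figure tells a reader that it would be missed less than 20% of the time. On the calculation below it would be missed 33–40% of the time. A non-significant interaction would then carry less information than the protocol suggests.

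**Working it through.** **Inputs.** From the protocol: 184 per arm (Patient recruitment and procedures); significance level 0.05, overall effect 0.33 SD at 83% power, moderation effect 0.50 with equal subgroups (Sample size and power). Assumed: two-sided test, 0.50 in SD units, independent patients, no variance reduction from covariates.

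**1. Analysed number behind the overall figure.** Power = Φ(d·√(n/2) − 1.96).
- n = 184: 0.33 × √92 = 3.165; Φ(1.205) = 88.6%.
- n = 156: 0.33 × √78 = 2.914; Φ(0.954) = 83.0%.

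The stated 83% is reproduced with 156 per arm, about 15% below 184. The protocol does not state 156, so both numbers are carried forward.

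**2. A calculation compatible with the moderation figure.** Arm comparison inside one subgroup holding half the sample, effect 0.50 SD:
- 92 per arm: 0.50 × √46 = 3.391; Φ(1.431) = 92.4%.
- 78 per arm: 0.50 × √39 = 3.122; Φ(1.162) = 87.7%.

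Both exceed 80%.

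**3. The planned test.** Interaction over four equal cells of m: SE = √(4/m) SD; power = Φ(0.50/SE − 1.96).
- m = 92 (184 per arm): SE = 0.2085; 0.50/0.2085 = 2.398; Φ(0.438) = 66.9%.
- m = 78 (156 per arm): SE = 0.2265; 0.50/0.2265 = 2.208; Φ(0.248) = 59.8%.

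Noncentral-t versions give 66.7% and 59.5%. One-sided testing at 0.05 gives 77.4% and 71.3%, still below 80%.

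**4. Interaction detectable with 80% power.** 2.80 × SE = 0.58 SD (184 per arm) or 0.63 SD (156 per arm). Conversely, 80% power for 0.50 SD needs 4 × (2.80/0.50)² ≈ 126 per cell, which is 504 analysed patients.

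**5. Unequal race groups.** SE = √(sum of 1/n over the four cells). The enrolled mix is not given, so these are illustrations only. If it matched either end of the clinic range, was the same in both arms and had no third category:
- 44/56: 66% (184 per arm) or 59% (156 per arm).
- 73/27: 57% or 50%.

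An equal split with 10% classed as other (45/45) gives 62% or 55%.

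**The case against.** The strongest objection is that the protocol neither defines the 0.50 nor names the test, so the figure cannot be called an arithmetic error with certainty. The race example under Study aims is partly a within-group statement, and an effect of 0.50 inside one group would have more than 80% power. This stands as far as the figure's origin goes. A reader might infer from the match in step 2 that the authors powered a subgroup comparison. The match makes that possible but does not establish it. The objection does not rescue the sentence, which is offered for moderation analyses that the same article defines as interaction tests.

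Second, covariates could restore the power. Knowledge is measured at baseline and after the visit, and covariates explaining about 27% (184 per arm) to 38% (156 per arm) of outcome variance would bring it to 80%. For a single baseline measure that is a correlation of about 0.52 to 0.62 (√0.27 and √0.38). This is possible. But the power section assumes no such gain, and the analysis section enters a covariate only if it proves associated with both arm and outcome. Reading 0.50 as half the difference of differences gives over 99%, a poor fit to the stated figure, and this reading is stated nowhere.

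Third, moderation is exploratory and the article calls its results preliminary. That limits the consequence and is reflected in the severity, but it does not make a printed power figure right.

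**Conclusion.** The concern holds in limited form. If 0.50 is a difference of arm effects in SD units, the planned interaction test for the knowledge score has about 67% power with 184 per arm, or about 60% with 156, against a stated figure above 80%. This rests on a two-sided 0.05 test, equal subgroups, independent patients and no covariate gain. The lower value also rests on an analysed number inferred from the protocol's 83%, not stated in it.

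Three stronger conclusions are not supported:
- **All three primary outcomes.** A reader might apply 60–67% to each. Two are binary and no base rates are given, so for them the SD-scale result is only indicative. Clustering within four clinics is also left out.
- **A definite figure for race.** Power is lower with unequal groups or an other category, but the 44–73% describes clinic populations, not enrolled patients. The lower end is also close to balance.
- **A planned misreading of null results.** Nothing in the protocol says that a non-significant interaction will be taken as equal benefit. That is a risk for readers of the power claim, not a stated intention.

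Severity is moderate: the figure sets neither the sample size nor any primary test.

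**What to change.** Replace the moderation sentence under Sample size and power in one of two ways.

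- **If 0.50 is a difference of arm effects:** give the power of the interaction test for the knowledge score, or the interaction detectable with 80% power. State the analysed number per arm, the sidedness, and the independence and covariate assumptions. Under the assumptions used here, that is about 67% power for 0.50 SD with 184 per arm (80% at 0.58 SD), or about 60% with 156 (80% at 0.63 SD). Add that power for race is lower if the groups are unequal.
- **If 0.50 is an arm effect within one subgroup:** say so, and drop the claim of more than 80% power for moderation.

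In either case, a non-significant interaction should not be read as evidence of equal effects. The cost is one sentence and a less favourable figure. Design, sample size and primary analysis are unchanged.

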### Statistical analysis plan

We will examine the distributions of all variables to describe the characteristics of the study population. We will conduct analyses using *t*-tests, *χ*^2^ tests, and Pearson or Spearman correlation coefficients to assess the bivariate associations between the baseline characteristics and the outcome variables. Bivariate analyses will also be conducted to assess the associations between the study arm and baseline characteristics. Owing to any significant differences detected at the 0.05 level, the variables associated with both the study arm and the outcome of interest will be entered as covariates in subsequent analyses. To test the overall difference between the study arms on the primary outcomes, we will conduct logistic regression models (for provider-patient discussion — yes/no, screening intentions — likely/unlikely) and a linear regression model (for the screening knowledge score). Logistic regression analyses will also be conducted on the secondary screening outcomes (lung screening referral — yes/no, lung screening completion — yes/no). This study will explore potential moderators (e.g., race, health literacy, smoking status). That will be done by evaluating the presence of interactions between the moderators and study arm, one at a time, after adding them to the regression models described above. In sensitivity analyses, we will evaluate the robustness of our findings by using versions of the above models with generalized estimating equations (GEE). These models will use the sites as clusters, and assume an exchangeable working correlation structure.

For the qualitative analysis, we will use a deductive thematic analysis based on a priori PRISM constructs, with additional codes added as needed. Initial codes will be generated by two coders and each of the coders will review two transcripts for each sub-population (i.e., patient and provider) to reach a consensus on the coding framework and application of codes prior to splitting up the remaining transcripts.

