### Clinical setting and healthcare provider participants

MedStar Health, the largest not-for-profit health system in the Mid-Atlantic, includes more than 300 care locations including more than 60 ambulatory care centers, and primary and specialty care in academic medical centers and community-based clinics, 10 hospitals, and 33 urgent care clinics located in Baltimore, MD, Washington, DC, and Northern VA. This health system provides care to a diverse community which includes a large Black or African American population (44–73% in the participating clinics), and uninsured or underinsured individuals.

We will conduct the quasi-experimental study in partnership with four primary care, community-based ambulatory clinics within the MedStar Health system, matched on CT scanner on site (yes/no) and minority representation (> 40% Black or African American; Fig. 2). Clinic eligibility criteria include (1) clinic providers use the Message Center within MedConnect (Oracle Cerner); (2) > 400 patients who are 50–80 years old with a documented smoking history in the last 12 months; (3) > 40% African American patient population; and (4) a site champion who will serve as the primary point of contact for this study. The provider sample includes full- and part-time primary care providers at the participating clinics.

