This study will provide preliminary data on the effectiveness and feasibility of multilevel implementation strategies to improve lung screening utilization in an equitable manner. Future work will include a large 2 × 2 factorial, cluster randomized trial to compare the independent and overlapping contributions of the provider and patient implementation strategies. Study limitations include the quasi-experimental study design, which will limit the ability to determine causality. Second, we considered recruiting all potentially eligible patients irrespective of having an upcoming appointment, as those with a scheduled appointment may be sicker and/or more engaged in their healthcare. However, a primary endpoint is whether the provider-level prompt and the patient-level activation impact the discussion about lung screening at the clinical encounter, and so we elected to include an upcoming appointment as an eligibility criterion. It is well documented that the collection of smoking-related data (e.g., smoking duration, cigarettes per day, pack-years) in the EHR is not standardized and is often incomplete. The proposed study will use the EHR data to identify potentially eligible individuals based on age (50–80 years old) and smoking status (current and former). However, there will be a high number of screen failures as well as patients who may be eligible for lung screening but are not approached for the study due to data missingness. In other ongoing work, our research team is conducting a quality improvement project to improve how tobacco use is assessed and documented in the primary care setting across MedStar.

Following the successful completion of this study, future work will include partnering with an expanded number of primary care practices and utilizing a cluster randomized controlled trial to determine if these implementation approaches facilitate an increase in lung screening rates equitably.

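### Covariates enter only if significant at 0.05 against both arm and outcome, so in this non-randomised comparison modest measured imbalances will often go unadjusted

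*Protocol article*

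**What the plan says.** The Statistical analysis plan section sets up two bivariate screens. The first is run "to assess the bivariate associations between the baseline characteristics and the outcome variables". The second is described as follows: "Bivariate analyses will also be conducted to assess the associations between the study arm and baseline characteristics". The resulting rule is that "the variables associated with both the study arm and the outcome of interest will be entered as covariates in subsequent analyses". Its threshold is given in the opening words of that sentence: "Owing to any significant differences detected at the 0.05 level". No covariate is named as always included. The GEE sensitivity analysis refits the same models with sites as clusters and does not change how covariates are chosen. Race, health literacy and smoking status are added one at a time as moderators; none is fixed in the main arm contrast.

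Table 1 lists the candidate covariates: "Demographics, social determinants of health, tobacco behaviors, cancer screening history, psychological variables". Baseline knowledge and intention are also measured at T0.

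Under Clinical setting and healthcare provider participants, the four clinics are "matched on CT scanner on site (yes/no) and minority representation", the latter defined as above 40% Black or African American. Clinic eligibility criterion 3 in the same section requires more than "40% African American patient population". The participating clinics are reported to range from 44% to 73%.

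**The concern.** Bias from an omitted covariate depends on the size of its imbalance multiplied by its effect on the outcome. Whether either association reaches p < 0.05 is a separate question, governed largely by sample size. A rule that needs both tests to be significant leaves out moderate imbalances that still shift the contrast. It can also give discussion, intention, knowledge, referral and completion different adjustment sets chosen from the data, and the reported standard errors treat each set as if it had been fixed.

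In a randomised trial this would mostly cost precision. Here it can cost validity. Matching offers limited help: with the same 40% cut used for eligibility and for matching, every eligible clinic falls in one category, so the factor as stated does not separate clinics within the 44–73% range. Because the article states the rule explicitly, this is a rule that is fixed badly and not a detail left to a fuller document.

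**Working it through.** **Inputs from the article:** 184 per arm; 0.05 for each screen (taken as two-sided, since sidedness is not stated); target effect 0.33 for knowledge with 83% power. **Assumed inputs:** imbalance and slope sizes, which the article does not give.

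**1. The plan's own figure.** Power ≈ Φ(d√(n/2) − 1.96).
- d = 0.33, n = 184: Φ(3.165 − 1.960) = 88.6%.
- d = 0.33, n = 156: Φ(2.915 − 1.960) = 83%.

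So 83% reproduces at 156 per arm, and 156/0.85 ≈ 184. The 15% loss this implies is not stated in the article. The 156 is therefore an inference, and 184 is used below unless noted. The power figure does not itself bear on the covariate rule.

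**2. How often the arm test flags a true imbalance (184 per arm).** Same formula:

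| True imbalance (SD) | Flagged |
|---|---|
| 0.10 | 16% |
| 0.15 | 30% |
| 0.20 | Φ(1.918 − 1.960) = 48% |
| 0.25 | 67% |
| 0.30 | 82% |

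For a binary factor at 50% versus 60%: (0.10 − 1.96 × 0.0519)/0.0516 = −0.03, and Φ(−0.03) = 49%. For 44% versus 73% it is essentially 100%.

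**3. Passing both tests.** The outcome test (N = 368) has 48% power at a correlation of 0.10 and 97% at 0.20. In simulation at 184 per arm with slopes of 0.1 to 0.4, a variable with a 0.2 SD imbalance passes both tests 25% to 48% of the time, so it goes unadjusted in 52% to 75% of studies. At 0.3 SD it passes 38% to 82% of the time.

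**4. Consequence for the arm contrast.** Simulation with no true arm effect, independent patients, outcome SD about 1, each covariate 0.2 SD apart with slope 0.25. With no adjustment, each covariate contributes 0.2 × 0.25 = 0.05 SD, so five in the same direction give 0.25 SD.

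| Scenario under the plan's rule | Residual bias (SD) | Type I error |
|---|---|---|
| One confounder, 184/arm | about 0.02 | about 5% |
| Five, three up and two down | about 0.02 | about 5% |
| Five, random directions, 184/arm | averages 0 | 6.4% |
| Five, same direction, 184/arm | about 0.08 | about 12% |
| Five, same direction, 156/arm | 0.09 | about 13% |

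Entering the full set every time gives bias of about 0 and type I error of about 5%. With five predictors at 156 per arm, the standard error is 0.097 against 0.108 under the rule, about 10% smaller.

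The rule does better than its selection rate suggests. At 48% selection, a naive figure for one confounder would be 0.52 × 0.05 = 0.026 SD; the simulated value is lower because the samples in which the test misses tend to be those with smaller realised imbalance.

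**5. Scale.** 0.08/0.33 = 24% of the knowledge target in the worst case shown; 0.02/0.33 = 6% in the milder ones.

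**The case against.** The best defence is that the rule works where it matters most: large imbalances are usually detected, and those missed are small. This is largely right. With one confounder, or several that partly cancel, the harm is slight. The larger figures need several modest confounders pushing the same way, and their sizes are assumed. The Discussion also concedes the design's limits ("Study limitations include the quasi-experimental study design, which will limit the ability to determine causality") and calls the data preliminary. That lowers the stakes but does not justify a selection rule that a fixed set outperforms.

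Three stronger readings are tempting and not supported.

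- *A large race gap would go unadjusted.* A 20-point gap in race with a 15-point outcome difference gives 0.20 × 0.15 = 3 points of bias only if nothing is adjusted. Under the plan's rule the arm test flags such a gap 97–98% of the time at 184 per arm, and the simulated residual bias is about 0.1 to 0.2 point.
- *Leaving out CT on site causes bias.* A factor balanced by matching does not confound. Omitting it costs precision at most, and if enrolment unbalanced it, the arm test could pick it up.
- *The arms may differ as 44% versus 73%.* That range describes individual clinics' patient populations, not arms or enrolled participants. The article does not say how the four clinics divide by race between arms, and even two clinics per arm is an inference. Fig. 2 is not available here.

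**Conclusion.** The point holds for small to moderate measured imbalances, up to about 0.2 SD or about 10 points in a binary factor. These will often stay out of the model. The cost depends on how many such covariates there are and whether they align: from almost nothing up to about a quarter of the knowledge target, with type I error roughly doubled. Table 1's many candidate domains make several modest confounders plausible, but the article gives no figures that would place this study within that range.

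The results assume independent patients, normal covariates and no unmeasured clinic effects. A fixed set removes bias from the measured covariates it contains; with four clinics it cannot remove differences between clinics, so it should not be presented as making the comparison unconfounded. The matching remark is a matter of description: the text supports a claim of matching on CT on site, but not on racial composition within the eligible range.

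**What to change.** - Delete the significance screen and state a short covariate set before analysis, drawn from Table 1: race, age, education, smoking status and prior screening history. For knowledge and intention, add the baseline value of that outcome, which is likely to be a strong predictor.
- For referral and completion, prespecify a smaller set or penalised logistic regression. Completion rates are not stated; at the 3–20% utilisation cited in the Abstract, 368 patients would give about 11 to 74 events (0.03 × 368 to 0.20 × 368), too few at the lower end for a full set.
- Keep the moderation analyses as planned; where the moderator is already in the model, only the interaction is added.
- Report balance between arms as standardised differences and not as p-values.
- Describe the clinics as effectively matched on CT on site only, and report each arm's racial composition.

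The cost is a change of wording: the measures are already planned, and no extra patients are needed. The downside is a few degrees of freedom and a limit on the number of covariates for sparse outcomes.
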